### Blood tests

The nurse will take peripheral venous blood from the participant’s forearm after fasting for more than 10 h in the morning. The blood samples will be sent out for measurements of haematology and biochemistry markers, high-sensitivity C-reactive protein (hsCRP), and homocysteine levels. Additionally, 5 mL of blood will be centrifuged at 2500 rpm for 15 min at 4 °C to obtain serum and plasma, then stored in the −80 °C freezer for later analysis. The Luminex-MultiDTX technology will be used to detect inflammatory markers in plasma. Telomere length and Mitochondrial DNA copy number will be measured using DNA samples with quantitative real-time polymerase chain reaction (q-PCR). Each reaction will be performed in triplicate and expressed as 2(-ΔΔCt).

### Body composition

This study will use the InBody 770 (Biospace, Korea), a body composition analyzer based on bioelectrical impedance analysis (BIA), to measure body composition. Participants are required to remove their coats and shoes, take off any metal accessories, and wear light clothing during the measurement. They will stand on the platform, grasping the hand electrodes with both hands and ensuring that their heels and the balls of their feet are properly placed on the foot electrodes. The body composition indicators used in this study will include body mass index (BMI), waist-to-hip ratio, skeletal muscle mass, skeletal muscle index, body fat percentage, visceral fat area, and phase angle.

### Statistical analysis

This study will follow the intention-to-treat principle for statistical analysis, including participants who complete baseline assessments and at least one follow-up assessment in the final analysis. Normally distributed continuous variables with a normal distribution will be presented as mean ± standard deviation, while non-normally distributed continuous variables will be presented as median (interquartile range). Categorical variables will be presented as frequencies and percentages (%). For the baseline data comparison between the control group and the intervention group, independent samples t-test will be used for normally distributed continuous variables, Mann-Whitney U test for non-normally distributed continuous variables, and chi-square test or Fisher’s exact test for categorical variables. Repeated measures analysis of variance will be used to analyze the changes in primary and secondary outcomes within the intervention and control groups, with multiple comparisons corrected using Bonferroni adjustment. Repeated measures analysis of covariance will be employed to compare the differences in primary and secondary outcome measures between the intervention and control groups at different follow-up times. The statistical analysis will be conducted using R language version 4.0.3 and SPSS 25.0 statistical software. Hypothesis testing will be conducted using two-tailed tests with a significance level of α = 0.05, where *p* < 0.05 is considered statistically significant.

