## Methods

### Study design

The MIDA study employs a Zelen-design for randomized controlled trial [26], which combines elements of an observational study with post-randomization informed consent and a randomized controlled trial. The cognitive, exercise, and nutritional interventions in the multidomain approach require close participant cooperation under the guidance of healthcare professionals, especially in individual home-based interventions. Maintaining blinding of assigned groups to participants poses a challenge. Furthermore, traditional randomization methods may result in decreased participant compliance, increased attrition rates, and higher demands for sample size and funding. Therefore, the Zelen-design is suitable for randomized controlled trial where maintaining blinding is difficult. It allows participants to provide further informed consent based on individual circumstances post-randomization. The Zelen-design can enhance compliance with follow-up procedures, align with real-world clinical settings, and better reflect clinical practice realities.

This study employed the Proactive Health Management Platform for Older Adults (SilverHealth Pro Platform, SPP), which was developed by the Fujian Provincial Center for Geriatrics. This study protocol has been approved by the Ethics Committee of Fujian Provincial Hospital (K2023-04-039) and registered with the Chinese Clinical Trial Registry (ChiCTR2300072010). The trial protocol is in accordance with the CONSORT guidelines [27].

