### Inclusion and exclusion criteria

Inclusion criteria: (1) aged between 60 and 85 years old; (2) living in the community; (3) a smartphone user.

Exclusion criteria: (1) severe neurological disorders (e.g. Alzheimer’s disease, vascular dementia, Parkinson’s disease, history of stroke with significant residual disability), severe psychiatric disorders (e.g. active major depressive disorder, schizophrenia or bipolar disorder), or moderate to severe cognitive dysfunction (MiniMental State Examination score ≤ 20); (2) conditions causing significant motor function impairment (e.g. severe arthritis, spinal cord injury, or muscular dystrophy), or recent fractures or surgeries within the past 6 months that limit mobility; (3) severe speech, language, hearing, or visual impairments that hinder communication with study personnel or participation in the intervention; (4) inability to perform basic activities of daily living independently, as defined by a Barthel Index score ≤ 40 or a Katz Index score ≤ 2; (5) terminal malignant diseases with a life expectancy of less than 6 months; (6) inability or unwillingness to provide informed consent or agree to follow-up.

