### Randomization, blinding, and allocation concealment

Participants who meet the inclusion and exclusion criteria will be randomized into intervention and control groups in a 1:1 ratio. The randomization process will be carried out by a data custodian not involved in the study. The data custodian will generate a set of random numbers using a simple randomization procedure and place into sequentially numbered, sealed, opaque envelopes. The random numbers will be assigned to participants in numerical order. Participants in the intervention group will be informed about the intervention procedure and follow-up plan, while participants in the control group will be informed about the follow-up plan. If participants agree to their assigned plan, they will sign the informed consent and undergo further baseline assessment.

Due to the difficulty of blinding intervention implementers and participants in a multidomain intervention, data collection personnel and statistical analysts will be blinded to reduce bias. Participants are instructed not to disclose their group assignment to anyone during baseline and follow-up assessments.

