### Outcome measures

Trained data collectors will conduct questionnaires and physical examinations with the participants. Additionally, the participants will undergo blood tests and body composition analysis. Data will be collected at three different times: post-randomization baseline, 6-month, and 12-month timepoints. The flowchart of the study protocol is displayed in Figure 2. Data collectors and data entry personnel neither participate in the intervention nor are aware of the participants’ group assignments.

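### The set labelled intention-to-treat drops people who decline their disclosed arm or never return, so it is a modified, available-case set and does not compare the groups as randomised

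*Protocol article*

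**What the plan says.** The Study design section describes a Zelen design that "combines elements of an observational study with post-randomization informed consent and a randomized controlled trial". The order of steps is in the section on randomization, blinding and allocation concealment:

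- Eligible people are allocated first: "Participants who meet the inclusion and exclusion criteria will be randomized into intervention and control groups in a 1:1 ratio".
- They are then told about their own arm only. For the active arm, "Participants in the intervention group will be informed about the intervention procedure and follow-up plan"; the control arm hears only about follow-up.
- Consent and baseline come last and depend on acceptance: "If participants agree to their assigned plan, they will sign the informed consent and undergo further baseline assessment".

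The Outcome measures section confirms the timing: "Data will be collected at three different times: post-randomization baseline, 6-month, and 12-month timepoints". The Statistical analysis section invokes the intention-to-treat principle and, in the same sentence, restricts the analysis by "including participants who complete baseline assessments and at least one follow-up assessment in the final analysis".

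Exclusion criterion 6 removes people for "inability or unwillingness to provide informed consent or agree to follow-up", and the criteria are applied before randomisation. The article does not say that people who decline their arm are kept in it, followed or counted.

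**The concern.** A Zelen design keeps a randomised comparison only if everyone allocated is analysed in the assigned arm, whether or not they accept what is offered. Here acceptance, baseline and return all come after the arm is known, and all three are conditions for being analysed.

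The two arms are also asked for very different things. The intervention arm is offered twelve 120-minute group sessions (the Discussion says ten, and the two must be reconciled) plus home training and diet logs three times a week. The control arm is offered six monthly lectures. If people with less energy, poorer health or less motivation decline the heavier offer more often, the analysed intervention group is a selected one, and part of any difference in change could reflect that selection.

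A second, smaller matter is that participants know their arm when baseline is measured. That can affect measures that depend on effort or mood, such as handgrip, some Fried items and the GDS-15. These are secondary or other outcomes, or components of them.

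**Working it through.** **Structure.** Put together, the sections on randomization, outcome measures and statistical analysis define the analysed set as: randomised, and accepted the disclosed arm, and completed the post-randomisation baseline, and attended at least one follow-up. Only the first condition is independent of the allocation. That the label does not fit the set follows from the text alone and needs no arithmetic.

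**The plan's own figure.** The sample size section starts from 74 per group at 90% power and allows for 20% dropout and 75% adherence: 74 / (0.80 × 0.75) = 123.3, rounded up to 124 per group, or 248. This reproduces the stated total. It has no term for refusal after allocation, and the text does not settle whether the 248 are counted at randomisation or after consent.

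**Yardstick (derived, not stated).** The article gives no SD. With the two-sample formula at two-sided 0.05 and 90% power, 74 per group implies (1.960 + 1.282) × √(2/74) = 0.533 SD.

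**Illustration.** The following are assumptions, because the documents give neither refusal rates nor outcomes in decliners:

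- control refusal 5%; intervention refusal 20%, 30% or 40%;
- decliners' 12-month change worse than accepters' by g = 0.2 or 0.5 SD, the same gap in both arms;
- no true effect, and 20% dropout in both arms.

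Within an arm with refusal r, the mean change among accepters exceeds the mean of all randomised by r × g. So bias = (r_int − r_ctl) × g. For example, (0.40 − 0.05) × 0.5 = 0.175 SD.

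The rejection probability is 1 − Φ(1.96 − bias/SE) + Φ(−1.96 − bias/SE). Two cases are shown:

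- **A:** 124 per arm counted after consent, so 124 × 0.8 ≈ 99 per arm are analysed and SE = √(2/99) = 0.142.
- **B:** 124 per arm randomised, so refusal also reduces n. The control arm has 124 × 0.95 × 0.8 = 94.2, and the intervention arm has 79.4, 69.4 or 59.5. SE = 0.152, 0.158 or 0.166.

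| g (SD) | Intervention refusal | Bias (SD) | Share of 0.533 | Error, case A | Error, case B |
|---|---|---|---|---|---|
| 0.2 | 20% | 0.030 | 6% | 5.5% | 5.4% |
| 0.2 | 30% | 0.050 | 9% | 6.4% | 6.2% |
| 0.2 | 40% | 0.070 | 13% | 7.8% | 7.1% |
| 0.5 | 20% | 0.075 | 14% | 8.2% | 7.8% |
| 0.5 | 30% | 0.125 | 23% | 14.2% | 12.4% |
| 0.5 | 40% | 0.175 | 33% | 23.4% | 18.5% |

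With equal refusal and the same kind of person refusing in each arm, the bias is zero and the error stays at 5%.

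**The case against.** *Direction and size are not shown.* This stands. Participants are volunteers who registered themselves, and people unwilling to consent or be followed are excluded beforehand, so refusal could be low. Some may refuse or leave a lecture-only arm because they wanted the programme. Outcomes are changes, and healthier people have less room to improve on a 0 to 5 frailty score. A reader might infer that every outcome is certain to favour the programme; the documents do not support that. The 0.5 SD gap is also a demanding assumption, almost as large as the implied planned effect, which is why 0.2 SD is shown beside it.

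*Covariate adjustment will deal with it.* In part. The planned repeated measures analysis of covariance can adjust for measured imbalance among those analysed, and it does not need decliners' data for that. Unmeasured differences such as motivation remain.

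*Knowledge of the arm contaminates the baseline.* A reader might extend this to the primary outcome. DNA methylation does not depend on effort or mood, so the point is confined to the secondary and other outcomes named above.

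*Criterion 6 already screens willingness, and the Study design section speaks of further consent.* An earlier general agreement may exist, so a flat contradiction is not established. It would not cure the problem: refusal of a particular arm can occur only once that arm is known, and baseline still depends on accepting it.

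*Modified intention-to-treat sets are common.* Those that drop people for lack of follow-up are. This one also drops people who reject the allocation itself, and it is not named as modified.

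**Conclusion.** The point holds as a matter of design and labelling. The analysis described is not intention-to-treat, and the groups compared are not the groups as randomised, for the primary outcome as for the others. Whether this produces bias depends on refusal and loss differing by arm in ways related to outcome. The unequal demands make that plausible, most likely in favour of the programme, but nothing in the documents establishes it.

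On the stated assumptions, the bias is 0.03 to 0.175 SD, about 6% to 33% of the 0.53 SD back-calculated from 74 per group. The nominal 5% error becomes about 5.5% to 8% (g = 0.2) or 8% to 23% (g = 0.5) with 99 per arm analysed. If refusal also reduces n, the ranges are about 5.4% to 7% and 8% to 18%. The 23% is the top corner of the grid, not an estimate for this trial.

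**What to change.** **If the order can still be changed.** Take consent to assessment and follow-up, and complete the baseline visit with a stored blood or DNA sample, before the envelope is opened. The arm-specific consent to the programme can follow, which keeps the Zelen element. Keep everyone randomised in the assigned arm, invite those who decline the programme to the 6- and 12-month visits, and define the intention-to-treat set as all randomised.

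**If it is too late.**

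- Rename the present set modified intention-to-treat.
- Report decliners and losses by arm.
- For frailty and intrinsic capacity, use the screening values listed in Table 1 as the pre-allocation baseline. This does not help the primary outcome: Table 1 shows no epigenetic measure at screening.
- Add a sensitivity analysis for the excluded participants.

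**In either case,** reconcile exclusion criterion 6 with consent after randomisation, and say whether 248 counts people randomised or people consented.

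**Cost.** A protocol amendment, baseline and follow-up visits for some people who decline the programme, and some additional methylation arrays. The Blood tests section describes storing serum and plasma, so storage of a sample for DNA would need to be written in.

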### Calculation of sample size

Sample size was firstly established by taking reference from a intervention study with the similar primary outcome (epigenetic age acceleration) [28]. In this study, 57 subjects were randomized to intervention and 58 subjects to the control groups, with a significant reversal of 0.66 years for epigenetic age acceleration. Nevertheless, given the secondary outcome frailty might require more sample size to achieve a significant improvement (the steps in Fried criteria are quite big), we referenced a multidomain study with 6-month interventions and 12-month follow up about frailty reversal [13].

In our study, each group will have 74 subjects to have 90% power to detect significant differences at *p* < 0.05 in epigenetic age acceleration and frailty changes at the 12-month follow-up based on a mixed linear model. Moreover, we considered the 20% dropout rate and 75% adherence [17], a total of 248 individuals will be recruited with 124 individuals in each group to ensure the efficacy of the study. Participants will be matched for chronological age, gender, smoking status, BMI for each group.

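### The named repeated-measures ANOVA/ANCOVA does not fit the stated analysis set, which admits a missing follow-up, or the mixed model behind the sample size

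*Protocol article*

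**What the plan says.** Three statements in the protocol article bear on this.

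- **Analysis set** (Statistical analysis): under an intention-to-treat label, "including participants who complete baseline assessments and at least one follow-up assessment in the final analysis". The Outcome measures section sets assessments at baseline, 6 months and 12 months, so a participant may miss either follow-up and still belong to the set.
- **Method** (Statistical analysis): "Repeated measures analysis of variance will be used to analyze the changes in primary and secondary outcomes within the intervention and control groups". For the between-arm comparison, "Repeated measures analysis of covariance will be employed to compare the differences in primary and secondary outcome measures between the intervention and control groups". The section names no mixed model and no handling of missed visits. It lists R and SPSS without assigning a procedure to either.
- **Sample size** (Calculation of sample size): "each group will have 74 subjects to have 90% power to detect significant differences at" the 5% level, "in epigenetic age acceleration and frailty changes at the 12-month follow-up based on a mixed linear model". For the inflation to 248, "we considered the 20% dropout rate and 75% adherence".

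**The concern.** The set and the method do not match. Classical repeated-measures ANOVA or ANCOVA works on a complete row of visits per person and removes incomplete rows. Moving baseline to the covariate side does not help, because the 6- and 12-month values are still both required. A person seen at baseline and month 6 only is in the set by definition but would contribute nothing to the result.

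The method also differs from the model on which the sample size rests. A mixed linear model uses whatever visits a person has, so it would suit the stated set. The Statistical analysis section does not mention it.

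What is at stake is who counts in the primary result. Participants are not blinded. The intervention arm has twelve two-hour group sessions under the Intervention group section, plus home training logged three times a week, while controls attend six lectures. Reasons for leaving may therefore differ between arms. A complete-case result is then open to attrition bias that a likelihood-based analysis of all visits would largely avoid, as long as dropout depends on values already observed.

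**Working it through.** **1. The plan's own figure.** Inputs from Calculation of sample size: 74 per group, 20% dropout, 75% adherence.

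74 / (0.80 × 0.75) = 123.3, rounded up to 124 per group and 248 in total. This reproduces the plan.

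The 74 itself cannot be checked, because no SD or within-person correlation is given. Solved backwards (two-sided α = 0.05, power 90%, normal approximation), it implies a standardised effect of (1.960 + 1.282) × √(2/74) = 0.533.

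**2. How many members of the set would be dropped.** Complete cases per arm: 124 × 0.80 = 99.2. The size of the set depends on when dropout occurs:

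| Timing of the 20% loss | In the set, per arm | Complete, per arm | Dropped, per arm |
|---|---|---|---|
| All after month 6 | 124 | 99.2 | 24.8 |
| Half before month 6, half after | 124 × 0.90 = 111.6 | 99.2 | 12.4 |

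People lost before month 6 who never return are outside the set under either method, so the loss would fall towards zero if all dropout were early. People who miss month 6 but return at month 12 would add to it.

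**3. Power.** At the implied effect with 99.2 per arm: 0.533 × √(99.2/2) = 3.753, and 3.753 − 1.960 = 1.793, which gives power of about 96%. It stays at 90% until about 40% of an arm is incomplete (124 × 0.60 = 74.4). This ignores any dilution of the effect by non-adherence, which does not depend on the choice between these two analyses.

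**4. Possible bias.** The documents give no correlations and no dropout mechanism, so everything here is assumed: 124 per arm, true effect −0.40 SD at both follow-ups, everyone seen at month 6, 20% lost afterwards, random loss in controls. In the intervention arm, loss depends logistically on the 6-month value or on the change from baseline to month 6. Visit correlations run from 0.6 to 0.85, with 3,000 simulated trials per setting. Two 12-month estimates were compared: a baseline-adjusted complete-case regression, and the maximum-likelihood estimate that also uses the 6-month data, as a mixed model would.

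| Log-odds of dropout per outcome SD | Complete-case estimate | Overstatement | Likelihood estimate |
|---|---|---|---|
| 0 (random) | about −0.40 | none beyond simulation error | −0.40 |
| 0.5 | −0.41 to −0.43 | about 4–7% | −0.40 |
| 1 | −0.43 to −0.45 | about 7–13% | −0.40 |
| 3 | −0.45 to −0.50 | about 13–26% | −0.40 |

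The top of the last row needs correlations of 0.6–0.7, dropout driven by change, and an odds ratio of e³ ≈ 20 per SD. Standard errors of the two estimates were nearly equal throughout (for example 0.115 and 0.113), so the gain from the mixed model lies in bias and coverage of the set, hardly in precision.

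**The case against.** **Deletion is inferred.** Nothing in the article says that incomplete cases are removed. Repeated-measures ANCOVA is sometimes a loose name for a mixed model, and both the sample-size wording and the analysis set would fit that reading. This stands as a limit on the claim: cases are dropped only if the method is fitted classically. It does not remove the mismatch, because the text names one method for the analysis and another for the power. If a mixed model was meant, saying so resolves the point.

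**The article is condensed.** Covariance structure and software procedure are commonly left to an analysis plan, and their absence is not criticised here. The point concerns two statements that the article does make and that do not agree.

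**Response-related dropout is doubtful for the primary outcome.** Nothing in the article says that participants learn their methylation-clock results, so dropout could follow them only indirectly, for example through health. This stands, and it is why the extreme scenario should not be taken as the expected size.

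**Stronger readings that the documents do not support.** A reader might infer that the 90% power is lost; about 99 complete cases per arm against 74 show otherwise. A reader might also take all of the planned dropout, 0.20 × 248 = 49.6 people, as deleted members of the set; that is a ceiling requiring every loss to fall after month 6. Finally, because the within-arm ANOVAs are described first, a reader might infer that they carry the conclusion. That is only sentence order: the between-arm comparison follows directly.

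**Conclusion.** The inconsistency is real and stands in the text. The named method, fitted classically, cannot use every member of the stated set, and it is not the model on which the sample size rests. Roughly 12 to 25 members of the set per arm would be lost at the planned dropout, provided that half or more of the losses come after month 6.

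The consequence is a departure from the declared intention-to-treat set and a possible, not a demonstrated, bias. The bias is zero under completely random dropout and modest under moderate response-related dropout confined to the intervention arm. It reaches about a quarter of the effect only under a mechanism that nothing in the documents supports. In every response-related setting tried, the error favoured the intervention. These sizes rest on assumed correlations, timing and mechanism, and on an assumed 0.40 SD effect. The likelihood estimate is protected only when dropout depends on observed values.

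**What to change.** In the Statistical analysis section, replace the repeated-measures ANOVA and ANCOVA with one baseline-adjusted linear mixed model for repeated measures per outcome. It should have arm, visit and arm-by-visit terms and use all available follow-up visits. State that the between-arm contrast at 12 months, with its confidence interval, is the primary result. Report within-arm changes only descriptively, from the same model.

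This matches both the analysis set and the sample-size section. The covariance structure, any further covariates and the model for the 0–5 frailty score can be left to the trial statistician. The wording should be settled before unblinded data are seen.

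The cost is wording only: N stays at 248, no new data are needed, and both named packages fit the model.
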